## Abstract

**Background:**

The COVID-19 pandemic has led to drastic increases in the prevalence and severity of insomnia symptoms. These increases in insomnia complaints have been paralleled by significant decreases in well-being, including increased symptoms of depression, anxiety, and suicidality and decreased quality of life. However, the efficacy and impact of early treatment of insomnia symptoms on future sleep and well-being remain unknown.

**Objective:**

Here, we present the framework and protocol for a novel feasibility, pilot study that aims to investigate whether a brief telehealth insomnia intervention targeting new insomnia that developed during the pandemic prevents deterioration of well-being, including symptoms of insomnia, depression, anxiety, suicidality, and quality of life.

**Methods:**

The protocol details a 2-arm randomized controlled feasibility trial to investigate the efficacy of a brief, telehealth-delivered, early treatment of insomnia and evaluate its potential to prevent deterioration of well-being. Participants with clinically significant insomnia symptoms that began during the pandemic were randomized to either a treatment group or a 28-week waitlist control group. Treatment consists of 4 telehealth sessions of cognitive behavioral therapy for insomnia (CBT-I) delivered over 5 weeks. All participants will complete assessments of insomnia symptom severity, well-being, and daily habits checklist at baseline (week 0) and at weeks 1-6, 12, 28, and 56.

**Results:**

The trial began enrollment on June 3, 2020 and closed enrollment on June 17, 2021. As of October 2021, 49 participants had been randomized to either immediate treatment or a 28-week waitlist; 23 participants were still active in the protocol.

**Conclusions:**

To our knowledge, this protocol would represent the first study to test an early sleep intervention for improving insomnia that emerged during the COVID-19 pandemic. The findings of this feasibility study could provide information about the utility of CBT-I for symptoms that emerge in the context of other stressors before they develop a chronic course and deepen understanding of the relationship between sleep and well-being.

**Trial Registration:**

ClinicalTrials.gov NCT04409743; https://clinicaltrials.gov/ct2/show/NCT04409743

**International Registered Report Identifier (IRRID):**

DERR1-10.2196/34409

## Introduction

### Background

The COVID-19 pandemic and resulting mass home confinement have led to a significant increase in insomnia complaints [1-3]. Recent studies from around the world report the prevalence of moderate to severe insomnia symptoms during the pandemic to range from 17.4% to 33.7% [4-6], compared with 10% to 15% prepandemic [7,8]. The prevalence rate is even higher among health care workers, individuals with medical comorbidities, and individuals in close contact with the virus [9,10]. Many of these insomnia symptoms may have developed as a direct result of the pandemic and home confinement [11]. For example, increases in sleep disturbances were directly influenced by the increase in COVID-19–related deaths, supporting the relationship between pandemic severity and insomnia severity [12]. Additionally, the increase in insomnia complaints may also be in part due to the exacerbation of several established risk factors for insomnia emerging from the COVID-19 pandemic including increased loneliness, perceived stress, and screen time, together with decreased social connection and physical activity [13-16].

The observed increases in insomnia complaints are paralleled by significant decreases in well-being, including increased depression, anxiety, and suicidality and decreased quality of life [17-21]. Critically, prior research in a nonpandemic environment found that insomnia is not only highly comorbid with depression and anxiety but also a strong predictive factor in their development and prognosis [22,23]. Given these findings, it is possible that the increase in insomnia complaints following the pandemic may be directly contributing to the increased prevalence of depression and anxiety during the pandemic [17,18]. Thus, treating insomnia symptoms early may be one approach to improve well-being and prevent future depression during the COVID-19 pandemic.

Cognitive behavioral therapy for insomnia (CBT-I) is the gold standard, first-line, nonpharmacological treatment for chronic insomnia recommended by the American College of Physicians [24]. It has been proven safe and effective in adults across the lifespan, in individual [25] and group formats [26] and when delivered in person or via telehealth [27]. A recently published article [28] from the European Academy for CBT-I provided evidence supporting the efficacy of CBT-I to treat sudden-onset insomnia and the validity of telehealth-delivered CBT-I. There is evidence that CBT-I not only reduces sleep complaints in those with chronic insomnia but can also reduce depression, anxiety, and suicidality and improve quality of life [29-33]. There is further evidence demonstrating that the resulting improvements in insomnia symptoms mediate the changes in depression symptoms but not the reverse [34]. Although the literature on this is limited, taken together, this evidence suggests that providing a brief, telehealth-delivered CBT-I to individuals with newly developed, pandemic-onset insomnia complaints may not only improve sleep but also improve well-being. However, to our knowledge, there are no studies investigating whether CBT-I would be an effective early treatment for insomnia arising from a highly disruptive and stressful event, such as a global pandemic, or whether intervening early in insomnia symptom onset could help mitigate other negative mental health outcomes. Additionally, it remains unknown whether common risk factors (eg, loneliness, perceived stress, and screen time) for insomnia and poor well-being that have been exacerbated by the pandemic may impact the effectiveness of an early intervention for insomnia symptoms.

Typically, individuals with sleep disturbance do not seek treatment unless their condition develops into chronic insomnia. This delay in seeking insomnia treatment makes parsing temporal, mechanistic relationships between insomnia and well-being nearly impossible. However, lifestyle changes and stress associated with the COVID-19 pandemic created large-scale disturbances in psychological well-being and sleep. These circumstances provided a novel opportunity to study the relationship between sleep and well-being by deploying an early sleep intervention to treat insomnia symptoms that have not yet developed into chronic insomnia. These circumstances have thus provided a unique opportunity through a pilot study to respond to a public health crisis and explore the temporal interrelationship between new sleep disturbances and deterioration in well-being as well as to assess whether intervening early in sleep disturbances is enough to alter these trajectories. The findings of the pilot study, the protocol of which is detailed in this paper, will be integral for guiding larger-scale trials in nonpandemic settings.

### Objectives

Our feasibility, pilot study investigates the viability of an early treatment for insomnia symptoms to treat insomnia symptoms arising during the COVID-19 pandemic and determine pandemic-related risk factors for worsening well-being and sleep outcomes. We also assess the impact of the intervention on insomnia severity and well-being across 28 weeks.

We will accomplish these objectives by conducting a waitlist-controlled trial across 28 weeks to address 3 aims.

Aim 1 is to determine whether a brief, telehealth CBT-I reduces insomnia symptoms arising during the COVID-19 pandemic. We hypothesize that CBT-I will lead to improvements in insomnia severity, as measured by the Insomnia Severity Index (ISI) [35,36], across 28 weeks. We also hypothesize that fewer participants in the CBT-I group will meet the Diagnostic and Statistical Manual of Mental Disorders 5th Edition (DSM-5) criteria for insomnia disorder, compared with the waitlist control group at weeks 12 and 28.

Aim 2 is to determine whether brief, telehealth CBT-I mitigates negative mental health outcomes arising during the COVID-19 pandemic. We hypothesize that, compared with the waitlist control group, the CBT-I group will have an improved trajectory of well-being across 28 weeks and will have better well-being at weeks 7, 12, and 28. Additionally, we hypothesize improvements in insomnia symptoms will mediate improvements in well-being from baseline to weeks 6, 12, and 28.

Aim 3 is to determine whether risk factors for insomnia that might be aggravated during the COVID-19 pandemic predict worse insomnia and negative mental health outcomes at follow-up. We hypothesize that self-reported high levels of social isolation, perceived stress, sleep reactivity, and screen time and low physical activity at baseline will predict worse long-term outcomes at 12 and 28 weeks across both study groups.

## Methods

### Trial Design

#### Overall Design

We designed a 2-arm randomized controlled feasibility trial to investigate the efficacy of an early, brief, telehealth-delivered insomnia treatment to prevent adverse sleep and well-being outcomes. Participants with clinically significant insomnia symptoms (current ISI total score ≥10) that began during the pandemic were randomized to either a treatment group or a waitlist control group. Treatment consists of 4 telehealth sessions of CBT-I delivered over 5 weeks. Participants in the waitlist control group do not receive any study interventions during the 28-week primary assessment period. All participants complete assessments of insomnia symptom severity, depressive symptom severity, anxiety symptom severity, quality of life, and pandemic-related risk factors at baseline (week 0), weeks 1-6, week 12, week 28, and week 56 (Figure 1). Primary outcomes focus on weeks 6, 12, and 28.

This study design creates 2 study phases: a 28-week waitlist-controlled (primary assessment) period, which allows the assessment of the therapy compared with a treatment-naive group and a delayed-start (secondary assessment) period, during which participants originally assigned to the waitlist control group receive the study therapy and participants assigned to the treatment group no longer receive study treatment (Figure 2). This allows assessment of long-term changes in sleep and well-being between individuals who underwent an early behavioral intervention for insomnia and those who did not. Our innovative approach will help elucidate mechanistic pathways between sleep and well-being as well as provide a needed clinical response to the COVID-19 pandemic and resulting mental health crisis.

**Figure 1 figure1:**
[figure not shown]
Study flow for each treatment group from prescreening through the 56-week follow-up, with primary outcome time points occurring at weeks 6, 12, and 28. CBT-I: cognitive behavioral therapy for insomnia.

**Figure 2 figure2:**
[figure not shown]
Study design in which the period between week 0 to week 28 is the waitlist-controlled period in which the immediate treatment group (cognitive behavioral therapy for insomnia [CBT-I]) can be directly compared with the waitlist control group (no CBT-I). At 28 weeks, participants in the waitlist group begin therapy and become the delayed treatment group.

#### Randomization

Participants were randomized into either CBT-I or a 28-week waitlist control condition using stratification by biological sex at birth (male, female) and baseline insomnia severity (ISI ≥10, ISI <10) in a 1:1 ratio. Participants who dropped out of the study after randomization, but before the week 1 visit, were replaced in the randomization matrix. Our sample size estimates (see the Power Calculation section) accounted for this replacement.

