#### Recruitment, Enrollment Criteria, Screening, and Retention

Participants are adults in the United States aged 18 years or older who experienced new sleep disturbances after the start of the COVID-19 pandemic. Participants were recruited nationally through online postings, newsletters, and social media. A subset of participants was recruited from an ongoing survey-based observational study about sleep and well-being during the COVID-19 pandemic. All participants met the inclusion and exclusion criteria outlined in Textbox 1.

Interested participants completed online prescreening questions (Table 2) assessing insomnia symptoms before and after the pandemic began (March 1, 2020), insomnia symptom duration, any unstable medications, and seizure history. Participants who met the prescreening criteria (Table 2) were invited to a video call with study staff to further assess eligibility. During this call, a research coordinator explained details of the study procedures and obtained informed consent. Consenting participants and research staff obtaining consent signed the informed consent form via a RedCap survey with e-signature capabilities. Participants were emailed a copy of the signed consent form. After informed consent was obtained, a trained member of the study staff then administered clinical interviews to assess eligibility. Before ending the call, a research coordinator sent the participant a link to complete remaining online screening questionnaires at their own pace. After the participants completed all online screening questionnaires and screening interviews (described in the Measures section), the study team collectively determined if the inclusion and exclusion criteria were met.

During the screening session, sleep disturbance was assessed using the Duke Structured Interview for Sleep Disorders (hereafter referred to as Duke) [41] and ISI. Participants were excluded from the study if their reported sleep disturbance duration on the Duke began prior to the start of the pandemic or if another sleep disorder was primarily responsible for their symptoms. Two versions of the ISI were administered at screening: one assessing symptoms during the week before the pandemic began (past) and one assessing symptoms in the past 2 weeks (current). Participants were deemed eligible for the study if past ISI score was <10 and current ISI score was ≥10, as a score of 10 was found to be optimal in detecting insomnia in a community sample [36].

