Participants with current or past psychosis, bipolar disorder, or epilepsy were excluded from the study due to safety concerns. Manipulating sleep increases the risk of seizures [42], mania [43], and psychosis [44] in individuals with a history of these conditions. Further, the brief version of CBT-I utilized in this study has not been validated as a reliable therapy in these populations. We administered the Mini-International Neuropsychiatric Interview (MINI) [45] to screen for psychosis and bipolar disorder and took a basic medical history to screen for history of seizures.

Participants currently abusing substances or taking over-the-counter or prescribed medications for sleep were not permitted in the study. To participate, all other medications must have been stable for at least 3 weeks, and medical conditions must have been deemed stable for at least 3 months by the study clinicians. However, hypnotics and other medications or supplements used to treat sleep disturbance were not permitted to be used during participation in the study. We collected information about current medication use as part of a basic medical history and assessed substance abuse or dependence using the MINI.

For eligible participants, data collected at the screening time point (including surveys after the session) are used as baseline measures.

Criteria for study participation.

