**Inclusion Criteria**
Age 18 years or olderHaving access to the internet and an email addressAcute subjective complaint of sleep disturbance (Insomnia Severity Index [ISI] before the pandemic <10 and current ISI ≥10) that began after March 1, 2020 or the COVID-19 pandemic (as reported during interview)Living in the United StatesLiterate and fluent in EnglishWillingness to participate in the study, sign the consent, and complete majority of questionnaires

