#### Primary Analyses

Statistical analyses aim 1 is to determine whether a brief, telehealth CBT-I reduces insomnia symptoms arising during the COVID-19 pandemic. All primary analyses will be performed using the intention-to-treat principle. We will test whether CBT-I is superior to a waitlist control in reducing insomnia symptoms by using a mixed effects linear model with autoregressive error structure using intention-to-treat analysis with outcomes at time points 6, 12, and 28. Insomnia severity as measured by the ISI will be entered as the dependent variable with randomization group (2 levels), time point (weeks 0, 6, 12, and 28), and group-by-time interaction included as fixed effects. The model will also include a random slope. Several hypotheses (1.1a-d) will be tested using the described mixed effects model.

Hypothesis 1.1a is that individuals assigned to the CBT-I group will experience an improved trajectory of insomnia symptoms during the waitlist-controlled 28-week period relative to those assigned to the waitlist control group. This hypothesis will be tested using a likelihood ratio test of the coefficients of the time and group-by-time interaction of the aforementioned mixed effects linear model.

Hypotheses 1.1b-1.1d are that individuals assigned to the CBT-I group during the waitlist-controlled period will have lower insomnia symptoms compared with those assigned to the waitlist-control group immediately posttreatment (hypothesis 1.1b; week 6) and at the short-term (hypothesis 1.1c; week 12) and long-term (hypothesis 1.1d; week 28) follow-ups. These hypotheses will be tested using the aforementioned mixed effects linear model with independent likelihood ratio tests using the treatment coefficient for the posttreatment (hypothesis 1.1b; Δ_1_ in Figure 2), short-term (hypothesis 1.1c; Δ_2_ in Figure 2), and long-term (hypothesis 1.1c; Δ_3_ in Figure 2) follow-up time points.

We will also test whether CBT-I is superior to the waitlist control in preventing an insomnia diagnosis following treatment by using multiple logistic regression analysis.

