Hypotheses 1.2a and 1.2b are that individuals who were assigned to the CBT-I group will be less likely to have an insomnia diagnosis than those who were assigned to the waitlist control group at weeks 12 and 28. These hypotheses will be tested using 2 separate logistic regression models, one using the short-term (hypothesis 1.2a; 12 weeks) and one using long-term (hypothesis 1.2b; 28 weeks) follow-up insomnia diagnosis, as defined by the Duke, as the dependent variable, with treatment (CBT-I, waitlist) as the independent variable.

Statistical analyses aim 2 is to determine whether a brief, telehealth CBT-I improves well-being during the COVID-19 pandemic. We will test whether immediate CBT-I is superior to a waitlist control in improving depressive symptoms as the primary measure of well-being during the waitlist-controlled period (28-week duration) by using a mixed effects linear model with autoregressive error structure using intention-to-treat analysis. Depression severity, as assessed by the BDI-II, will be entered as the dependent variable with baseline covariates used for stratified randomization (ie, baseline insomnia severity and sex), group (immediate CBT-I or waitlist control), time point (weeks 0-6, 12, and 28), and group-by-time interaction included as fixed effects. The model will also include a random slope. Separate, secondary analyses will be conducted on the secondary measures relating to well-being described in the Secondary Outcomes section (eg, anxiety, suicidality, quality of life). Several hypotheses will be tested using this model.

Hypothesis 2.2a is that individuals assigned to the CBT-I group will have an improved trajectory of depressive symptoms across the 28 weeks relative to individuals assigned to the waitlist control group. This hypothesis will be tested using a likelihood ratio test of the coefficients of the time and group-by-time interaction terms of the aforementioned mixed effects linear model.

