This study was conceived and launched in response to the global pandemic of COVID-19, which, while rendering it novel, presents unique challenges. First, to address our scientific questions, we sought to recruit participants early in the course of their sleep disturbance, causing a significant urgency to launch the study. This time pressure led us to conduct this study with limited resources, which impacted our recruitment efforts. We were unable to offer compensation for participation. We relied heavily on recruiting participants through free online platforms, such as social media posts, online message boards, and electronic newsletters. Due to these recruitment concerns and the resulting decreased statistical power for the planned analysis, we view this as a feasibility study. Therefore, the planned analyses and publications resulting from this protocol will utilize effect size estimates, rather than statistical significance, to provide pilot and feasibility data to inform future hypotheses. A second potential limitation is the unequal attrition rate in the treatment versus the waitlist control group. Since participants are not financially compensated, the primary motivation of participation is meeting with a therapist on a weekly basis to address their sleep concerns. Thus, it is possible that individuals in the waitlist control group were more likely to decline to participate in follow-up time points due to loss of interest or spontaneous improvement in symptoms over time. Although this could potentially affect the ability to detect significant differences in between-group comparisons at the long-term follow-up time points due to inadequate power, our analytic approach using regression models has the advantage of increased efficiency and power over unadjusted analyses [63,64]. We will address this issue by assessing whether missingness is related to any observed covariates. If this is the case, an issue of greater concern is the potential bias in the estimate of the treatment effect if neither the missing completely at random (MCAR) nor the missing at random (MAR) assumption holds. Although mixed effects linear models lead to unbiased estimates of the treatment effect under the MCAR and MAR assumptions, estimates may be biased under nonignorable missingness. Further sensitivity analyses will be performed if this is the case.

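### The printed severity stratification factor (ISI ≥10 vs <10) has only one possible level given the eligibility criteria, and neither primary model makes clear how starting severity is adjusted for

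*Protocol article*

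**What the plan says.** The Randomization section names two stratification factors: biological sex, and "baseline insomnia severity (ISI ≥10, ISI <10) in a 1:1 ratio".

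Three places restrict who could be randomised. Overall Design: "Participants with clinically significant insomnia symptoms (current ISI total score ≥10) that began during the pandemic were randomized". Recruitment, Enrollment Criteria, Screening, and Retention: "Participants were deemed eligible for the study if past ISI score was <10 and current ISI score was ≥10". The Inclusion Criteria repeat the pair: "before the pandemic <10 and current ISI ≥10". The prescreening table (Table 2) applies the same two cuts. The recruitment section also fixes what baseline means: "data collected at the screening time point (including surveys after the session) are used as baseline measures".

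Under Primary Analyses, the aim 2 depression model includes "baseline covariates used for stratified randomization (ie, baseline insomnia severity and sex". The aim 1 ISI model has "randomization group (2 levels), time point (weeks 0, 6, 12, and 28), and group-by-time interaction included as fixed effects", plus a random slope, and no other terms are listed. The Discussion, on attrition, says "our analytic approach using regression models has the advantage of increased efficiency and power over unadjusted analyses".

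**The concern.** A stratification factor should split the randomised sample, and the printed one cannot. Either only sex was stratified in practice, or a different ISI cut was used and is misreported. The text needs correction in both cases.

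The problem carries into the analysis. The aim 2 model defines its severity covariate by reference to that factor. The aim 1 model leaves out even sex, the one factor that works, and does not say whether the arms share a week-0 mean. The article nevertheless counts on regression adjustment to offset lost power. With 26 and 23 participants randomised, and with Statistical Procedure and Data Analysis putting the emphasis on effect sizes and confidence intervals, starting balance and precision bear directly on what will be reported.

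**Working it through.** **1. Can the factor take two values?**
- Read as current ISI: everyone must score ≥10, so the <10 stratum is empty.
- Read as pre-pandemic ISI: everyone must score <10, so the ≥10 stratum is empty.
- Read as a later ISI: Data Collection places randomisation after eligibility is decided and before the week 1 meeting, and screening data serve as baseline. No later score could have been used.

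Of the four sex-by-severity strata, only two can be filled.

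**2. The plan's own power figure.** Inputs from Power Calculation: 25 per group, d = 0.80, 5% level (two-sided assumed, as sidedness is not stated). The noncentrality is 0.80 × √(25 × 25 / 50) = 2.83. The noncentral t (48 df) gives 79.1% and the normal approximation 80.7%, against the stated 80%. The figure reproduces and does not depend on the stratification.

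**3. Chance imbalance without a working severity stratum.** In baseline SD units, the difference in mean ISI between arms has SD √(1/26 + 1/23) = 0.286. The probability of an absolute difference above 0.5 SD is 2 × [1 − Φ(0.5/0.286)] = 8.1% (7.7% at 25 per arm). For comparison, a simulation with 25 per arm and a cut inside the eligible range gave SD 0.18 and a probability of 0.4%. It used an illustrative split at 15, with ISI assumed normal with mean 15 and SD 4, restricted to 10 and above.

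**4. The aim 2 covariate.** With intercept, group, sex and severity as columns and severity coded as the printed factor, the design matrix has rank 3 for 4 columns, so the severity coefficient cannot be estimated. With severity as the continuous ISI score, the rank is 4 and the term is estimable.

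**5. The aim 1 contrast.** Take complete data, equal variances across visits and separate week-0 means for each arm. The variance of the week-28 treatment contrast, relative to a raw difference between arms, then depends on how the contrast is defined and on the baseline-to-week-28 correlation ρ. The documents do not give ρ, so a range is assumed:

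| ρ (assumed) | raw difference | difference in change, 2(1−ρ) | baseline-adjusted, 1−ρ² |
|---|---|---|---|
| 0.3 | 1 | 1.40 | 0.91 |
| 0.4 | 1 | 1.20 | 0.84 |
| 0.5 | 1 | 1.00 | 0.75 |
| 0.6 | 1 | 0.80 | 0.64 |

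Adjustment has the smallest variance in every row. Against the raw difference it saves 9 to 36%. Against the change score the ratio is (1−ρ²)/[2(1−ρ)] = (1+ρ)/2, or 0.65 to 0.80, a saving of 35 to 20%.

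**6. In participants.** Trial Status and Timeline reports 34 who had completed week 28 and 3 still awaiting it. Relative to the raw contrast, 34/0.91 = 37 and 34/0.64 = 53. If all 3 complete, 37/0.91 = 41 and 37/0.64 = 58.

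**The case against.** The empty stratum has no good defence. The objections concern what a reader might build on it, and most of them stand.

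- A reader might infer that severity was left unbalanced. The documents do not show this. Allocation at 1:1 balances severity in expectation, and no baseline comparison is reported. What is missing is control by stratification.
- A reader might infer that the aim 2 covariate is a constant. That holds only for the binary coding. The section names baseline insomnia severity without fixing its form, and as a score it could run from 10 to 28.
- A reader might infer that aim 1 adjusts for nothing. Week-0 ISI is one of the modelled outcome times, so the group-by-time terms describe change from baseline, and under missing at random the model draws on earlier data from those who miss week 28. Whether the week 6, 12 and 28 tests are raw differences or changes depends on a parametrisation the article does not give.
- The Discussion sentence concerns attrition and speaks of regression models in general. It does not claim adjustment for severity, so it fits aim 1 poorly without strictly contradicting it.
- This is a feasibility trial, and the choice between a common baseline, a baseline covariate and unconstrained repeated measures is one of efficiency, not validity.

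The week-0 argument answers less than it seems to. With free week-0 means, neither reading of the contrast reaches the precision of adjustment at any correlation in the table. Dropout lets week 0 recover some information, but not the full gain.

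**Conclusion.** The point holds in limited form. As printed, the severity factor has one level, so stratification gave no control of severity balance beyond simple randomisation. The aim 2 covariate drops out if coded as that factor. Aim 1 lists no baseline covariate, omits sex and states no common-baseline constraint, which sits poorly with the efficiency the Discussion cites.

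The randomisation and the 80% power figure remain valid, and no bias is shown. Nor do the documents establish that sex alone was used, since the printed cut may itself be the error.

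The size is about an 8% chance of a baseline difference above 0.5 SD at 26 and 23, and a 9 to 36% variance saving on a raw week-28 contrast. The saving rests on the assumed correlation of 0.3 to 0.6, equal variances and complete data. Restricting entry to ISI ≥10 narrows the baseline range and argues for the lower half of that range.

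**What to change.** 1. Check the randomisation matrix and report the stratification actually used: sex only, or sex with the true ISI cut.
2. In the aim 2 model, specify severity as continuous week-0 ISI, alongside sex.
3. In the aim 1 model, add sex and settle how baseline enters. Either constrain the arms to a common week-0 mean, or use week-0 ISI as a covariate with weeks 6, 12 and 28 as the outcomes.
4. Declare the change as made after the week-6 interim analyses. Trial Status and Timeline says the primary hypotheses had not yet been tested in full, so the models can still be fixed ahead of the full analysis, but not as if no data had been seen.

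The variables are already collected. The cost is a few degrees of freedom (sex takes one, and a baseline-by-visit term over three visits takes three) and open disclosure of a post-interim change.
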